### Comparator

Participants in the comparison arm of the trial will be given the standard of care (dry cord care).

### Measurements

The main outcomes of this study are clinically diagnosed omphalitis and severe illness. Assessment for these outcomes is scheduled on days 1, 3, 7, 14 and 28 after birth. Further, the mothers are encouraged to visit our clinics if they observe any signs of umbilical cord stump infection or if they are worried that their child is otherwise ill. Severe illness is defined as illness that is associated with any of the following danger signs observed or verified by a study clinician: inability to feed or vomiting of all intake, lethargy or unconsciousness, severe lower chest in-drawing, axillary temperature of ≥37.5 °C or <35.5 °C, grunting, cyanosis, convulsions or a history of convulsions, and/or results in hospitalization and/or results in death. The data collection team records the presence or absence of omphalitis at each clinic visit. Signs for omphalitis include: pus, redness (inflammation) and swelling (edema) of the cord stump and the surrounding skin at its base. Swelling and redness is further broken down into four groups: none, mild, moderate and severe. No swelling or redness is defined as absence of visible swelling or redness; mild swelling or redness as that which is limited to the cord stump only; moderate swelling or redness as that extending less than 2 cm onto the abdominal skin at the base of the stump and severe swelling or redness as extending at least 2 cm or more around the abdominal skin at the base of the stump. Pus is characterized as being either present or absent. Cord infection is then defined based on combinations of these signs and their severity into four categories as follows: (1) redness extending to skin or pus, (2) moderate or severe redness, (3) moderate or severe redness with pus, or severe redness alone and (4) severe redness with pus [6, 7].

Given the necessity of the comparison arm to receive advice and education on dry cord care (the standard of care), this is an unblinded study. The study nurses are not made aware of the hypotheses that are being tested, and undergo rigorous training and standardization with respect to the assessment of omphalitis and severe illness to maintain a high validity in outcome assessment.

### Background characteristics and potential confounders

Using questionnaires and available records, data will be collected on several potential individual-level confounders. These include: maternal age, maternal education, antenatal care attendance, iron supplementation during pregnancy, antibiotic use during the last weeks of pregnancy, premature rupture of membranes, signs of chorioamnionitis, wealth, household size, parity, tetanus vaccination, gestational age, singleton or multiple birth, sex of the infant, birth weight, use of a clean delivery kit, prelacteal feeds, breastfeeding initiation time, infant’s receipt of colostrum, and Bacille Calmette-Guérin (BCG) vaccination. To further describe the population from which our participants are derived and to adjust for any contextual level confounders, we collect data using questionnaires on group/contextual-level factors such as the presence of electricity in the community, and residence (rural versus urban).

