### Intervention

The intervention is umbilical cord stump cleansing with a single application of 4% CHX solution at birth. The watery solution was obtained from Galentic Pharma in India (http://www.galentic.com) and came in packages of 10-ml dropper bottles. The application is provided by a trained health worker (nurse or midwife) at the health facility as soon as possible and no later than 12 h after birth. The solution is applied using the dropper bottle onto the tip of the infant’s umbilical cord stump, its base and the area of skin surrounding it. A CHX-moistened cotton ball is then used to gently cleanse the base of the stump and the surrounding skin. Health workers have been trained by general physicians and pediatricians to correctly, consistently and safely apply CHX. Five CHX containers will be randomly chosen early, during and towards the end of the trial to check for CHX concentration and antibacterial activity. The chlorhexidine stock is securely kept below 30 °C, away from light in tightly closed/sealed bottles.

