### Data collection and management

#### Data collection: primary objectives

Our study staff in the three study clinics identifies HIV-1-negative pregnant women in the delivery rooms. Potential participants are approached and informed about the study. Following a live birth, study procedures are explained to the women, and babies of those providing informed consent are enrolled and then randomized to either the intervention or comparison arm by research assistants, using the cell phone-based application described above. For enrolled infants, data will be collected using questionnaires on day 1, and on days 3, 7, 14 and 28 after birth (Fig. 1).

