### Data analyses

Baseline characteristics of the mothers, their households and the newborns will be compared between the intervention and comparison arms to check for comparability and identify potential confounders. Continuous variables will be summarized using means, medians, standard deviations and interquartile ranges while percentages will be used for categorical variables.

Analysis for both primary objectives will be based on intention-to-treat. Therefore, all infants randomized and enrolled into the study will be included in the final analysis regardless of whether CHX was applied to their umbilical cord stump and surrounding skin or not (Fig. 2: flow chart and Additional file 1: Standard Protocol Items: Recommendations for Interventional Trials (SPIRIT) Checklist). The risks of omphalitis and severe illness in the intervention arm will be compared to those in the comparison arm using binomial regression with a log link to obtain risk ratios (RR). Multivariable analysis will be used to take into account potential confounding. Only confounders whose inclusion in the model results in a substantial (>5%) change in the estimate of the main outcome will be maintained in the final model. Percent protective efficacy will be calculated as (1 − RR) × 100.

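### Four postnatal variables that may follow randomisation are listed as confounders, and the >5% change rule could bring them into the final model and bias the adjusted risk ratio

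*Protocol article*

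**What the plan says.** Under Background characteristics and potential confounders, the protocol article states that "data will be collected on several potential individual-level confounders". The list mixes variables settled by the time of delivery (maternal age, parity, gestational age, birth weight, sex) with "prelacteal feeds, breastfeeding initiation time", colostrum receipt and BCG. It does not mark which must be known before allocation.

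Under Data analyses, the arms are first compared by log-link binomial regression on an intention-to-treat basis. The text continues: "Multivariable analysis will be used to take into account potential confounding". The selection rule for the final model is given as: "Only confounders whose inclusion in the model results in a substantial (>5%) change in the estimate of the main outcome will be maintained in the" (the quote stops just before that model is named).

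On timing, the data collection section says that after a live birth and explanation of the study, "babies of those providing informed consent are enrolled and then randomized". The Intervention section has the solution applied "as soon as possible and no later than 12 h after birth". Questionnaires run on day 1 and on days 3, 7, 14 and 28. No section says when each of the four variables is fixed or recorded relative to randomisation.

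**The concern.** Randomisation removes systematic confounding by anything settled before allocation. A variable settled afterwards cannot be a confounder of the arm comparison. It can be a consequence of the outcome, a consequence of allocation, or neither, and adjusting for it is harmful in the first two cases.

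The article itself makes the first route plausible. Under Measurements, inability to feed is one of the danger signs that define severe illness, and outcome assessment starts on day 1. Feeding variables therefore overlap in content with a primary outcome, and a sick newborn may also miss or delay BCG. The second route is only possible: the trial is unblinded and the comparison arm receives advice on dry cord care, but no mechanism by which this changes feeding or vaccination is described.

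The retention rule adds to the problem. In a large 1:1 trial a true baseline covariate hardly moves the risk ratio, so a variable that does move it by more than 5% is more likely to be one that illness or allocation has changed. At stake is the adjusted risk ratio in the final model, and the protective efficacy if that is computed from it.

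**Working it through.** The article gives no figure for this bias, so there is none to reproduce. The check asks what the stated rule does under known conditions.

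**Inputs from the Sample size and Randomization sections.** Total 4760 with 5% attrition: 4760 × 0.95 = 4522, or 2261 per arm at 1:1. Control risk of severe illness 6%; a 30% reduction gives 0.06 × 0.70 = 4.2%, so the true RR is 0.70.

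**Assumptions.** All covariate prevalences and associations below are assumed, since the documents give none. Only severe illness was modelled, with one binary covariate at a time. The Mantel-Haenszel RR stands in for the adjusted log-binomial RR, except in the BCG scenarios, which used a Poisson log-link model. A covariate is kept if |RR_adj / RR_unadj − 1| > 0.05.

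**Step 1: a true baseline covariate** (30% prevalence, RR 2 for the outcome). The standard error of the chance imbalance is √(2 × 0.3 × 0.7 / 2261) = 0.0136. One standard error moves the RR by about 0.0136 / 1.3 = 1.0%, so a 5% shift is very rare. In 1,000 simulated trials the covariate was kept in 0.1%, and the final RR averaged 0.70.

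**Step 2: a covariate altered by illness, worked once by hand.** Suppose it is present in 20% of well and 80% of ill infants. Expected ill infants: control 2261 × 0.06 = 135.7; CHX 2261 × 0.042 = 95.0. RR_MH = Σ(a·n0/n) / Σ(c·n1/n), where a and c are the ill infants in the CHX and control arms, n1 and n0 the stratum sizes in those arms, and n = n1 + n0.

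| Covariate | a | n1 | c | n0 | a·n0/n | c·n1/n |
|---|---|---|---|---|---|---|
| present | 76.0 | 509.2 | 108.5 | 533.6 | 38.87 | 52.99 |
| absent | 19.0 | 1751.8 | 27.1 | 1727.4 | 9.43 | 13.66 |

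RR_MH = 48.30 / 66.65 = 0.725, against a true 0.70: a shift of 3.5% with no confounding present. Chance variation around 3.5% takes a sizeable share of trials past the 5% threshold.

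**Step 3: the same by simulation** (1,000 trials each; 20% in well infants).

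| Present in ill infants | Kept by rule | Unadjusted RR | RR after the rule |
|---|---|---|---|
| 40% | 0.2% | 0.693 | 0.693 |
| 60% | 12.5% | 0.694 | 0.699 |
| 80% | 39.8% | 0.701 | 0.722 |
| 95% | 52.8% | 0.705 | 0.736 |

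The unadjusted averages differ from 0.70 only by simulation error, so the comparison is within rows.

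**Step 4: BCG uptake.** With 90% uptake in well and 20% in ill infants (200 trials), adjustment moved the mean RR from 0.703 to 0.756, and BCG was kept in 66%. With 60% uptake in ill infants, it moved from 0.696 to 0.704, and BCG was kept in 8%. The 90%/20% case treats every illness to day 28 as able to prevent vaccination. If only half of illnesses come early enough (assumed), BCG is kept in 17% and the RR after the rule averages 0.714 against 0.707 unadjusted. If a quarter do, it is kept in 0.6%, with 0.702 against 0.702.

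**Step 5: a covariate shifted by allocation** (30% in control, lower by d with CHX; RR 2 for the outcome). Adjusting recovers only the part of the effect not passing through the covariate, 0.70 × 1.3 / (1.3 − d). For d = 0.10 this is 0.91 / 1.20 = 0.758; for d = 0.20 it is 0.91 / 1.10 = 0.827. In simulation the rule kept the covariate in 95.2% and 99.9% of trials, with final RRs of 0.76 and 0.83. At d = 0.05 it was kept in 21.4%, with a final RR of 0.71. This shows how the rule would behave if allocation did shift a covariate; the article does not show that it does.

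**The case against.** **Timing is not established.** A reader might infer that all four variables are fixed after allocation. The article does not show this. Consent and application may come up to 12 h after birth, so first feeds and prelacteal feeds may precede randomisation in many infants, and colostrum and BCG may fall on either side. This stands: the claim is that they may follow allocation and that nothing requires otherwise.

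**There is a baseline filter.** Data analyses opens by comparing baseline characteristics between arms to identify potential confounders, and the list can be read as data to collect, not as a model. Collecting feeding and BCG data also serves the stated aim of finding modifiable risk factors for omphalitis. But baseline is not defined there, and the four variables sit under a heading on background characteristics and potential confounders, so the filter does not exclude them. The final covariate set could be left to an analysis plan. Here, though, the article goes further: it names these variables as candidates and states the rule that admits them.

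**The main comparison is safe.** A reader might infer that the trial's intention-to-treat result is biased. The unadjusted RR is untouched, and the article does not call the adjusted RR the better one. It does call the adjusted model final, without saying which estimate leads.

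**The size depends on strong assumptions.** This also stands. Newborns needing hospitalisation immediately after birth are excluded, illness after vaccination cannot prevent it, and with weak dependence the shift disappears. The route through allocation has no documented mechanism.

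**Conclusion.** The point holds as a conditional one. The article admits as adjustment candidates four variables that may follow randomisation, and its retention rule favours those that illness or allocation has strongly changed over harmless baseline covariates. Only the adjusted RR is exposed.

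For a covariate altered by illness, with a true RR of 0.70, the shift runs from nothing (0.70 to 0.70) under weak dependence to about 0.72–0.76 under strong dependence. In efficacy terms, (1 − RR) × 100 falls from 30% to between 28% and 24%. The upper end needs the extreme BCG assumption. Every simulated shift was towards the null, so the risk shown is a diluted effect, not a false positive. These figures rest on assumed prevalences and associations, one binary covariate at a time, and the severe illness outcome only.

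The documents do not support saying that all four variables are post-allocation, that the primary comparison is invalid, or that material bias is expected.

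**What to change.** In Data analyses:

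- Limit adjustment to a prespecified set of variables fixed before randomisation: maternal and pregnancy factors, gestational age, birth weight, sex, multiplicity, delivery-kit use and centre.
- Drop the >5% change-in-estimate rule. Shortening the list alone would leave data-driven selection in place.
- State that the unadjusted RR, or the RR adjusted for that prespecified set, is primary.
- Report prelacteal feeds, breastfeeding initiation time, colostrum and BCG by arm in a descriptive table outside the effect models. They remain available for the risk-factor work.

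The cost is a small edit to the analysis text, with data collection unchanged. No legitimate control of confounding is lost: in the simulation a pre-allocation covariate left the RR at 0.70. Recruitment has been under way since July 2016, so the change should be documented before outcome data are examined by arm for the final analysis.

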### Sample size

Sample size for primary objective 1: with type 1 error set at 5%, type 2 error at 0.2 (i.e., 80% power), and accounting for 5% attrition, a sample size of 4760 children will be required to detect a 30% relative reduction in the incidence of severe illness following a single cleansing of the umbilical cord stump with the 4% CHX solution. We assumed a 6% risk of severe illness in the control group.

Power calculation for objective 2: setting the type 1 error at 5% and accounting for 5% attrition, a total sample size of 4760 children will yield 96% power to detect a 30% relative reduction in the incidence of omphalitis following a single cleansing of the umbilical cord stump with the 4% CHX solution. The assumed risk of omphalitis in the dry cord care group (comparator) is 11.5% based on recently published data from the trial in Pemba [10].

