### Randomization

For each of the three health centres, a computer-generated random sequence list with permuted blocks of varying size (4, 6 or 8) was generated by CISMAC scientist [name], who is otherwise not involved in the trial. Based on this sequence, children are randomly allocated to intervention or comparison arms in a 1:1 ratio. Concealment is by a cell phone-based application that yields the trial arm allocation only after consent for inclusion has been confirmed.

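### The 4,760 children stated for severe illness do not contain the full 5% attrition allowance: after 5% loss, power for a 30% reduction is about 78–79%, not 80% (a minor shortfall)

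*Protocol article*

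**What the plan says.** The Sample size section of the protocol article treats the two primary objectives differently.

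- Severe illness (objective 1) sets the size of the trial. The inputs are "with type 1 error set at 5%, type 2 error at 0.2 (i.e., 80% power), and accounting for 5% attrition", a 30% relative reduction, and a control risk given as "We assumed a 6% risk of severe illness in the control group". The output is a total of 4,760, described as the number required with attrition already counted: "accounting for 5% attrition, a sample size of 4760 children will be required to detect a 30% relative reduction in the incidence of severe illness".
- Omphalitis (objective 2) takes that total as given and reports the resulting power: "a total sample size of 4760 children will yield 96% power to detect a 30% relative reduction in the incidence of omphalitis", again after 5% attrition, from an assumed control risk of 11.5%.

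The Randomization section adds that "children are randomly allocated to intervention or comparison arms in a 1:1 ratio". The Data analyses section says the arms will be compared "using binomial regression with a log link to obtain risk ratios (RR"). The article does not state whether the 5% type 1 error is one- or two-sided, nor which sample-size formula was used.

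**The concern.** For objective 1 the power is fixed at 80% and the sample size is the result, so the sample size is the figure to check. Every numerical input except sidedness is printed, and the total lies close to what those inputs require before any allowance for loss. If so, the sentence claims an allowance that the number does not fully carry.

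Severe illness is the first primary objective and the outcome on which the trial is sized. Readers of the eventual result will take the stated power as the design's power under the stated loss, so the figure should follow from its own inputs.

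**Working it through.** **Inputs.** Control risk p1 = 0.06; 30% relative reduction, so p2 = 0.7 × 0.06 = 0.042; type 1 error 5%; power 80%; attrition 5% (all from Sample size). Allocation 1:1 (Randomization). Assumption: two-sided test, so z = 1.960 for the type 1 error and 0.8416 for the power.

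**Step 1: evaluable children needed, pooled two-proportion formula.** Mean risk = 0.051.

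n per arm = [1.960 × √(2 × 0.051 × 0.949) + 0.8416 × √(0.06 × 0.94 + 0.042 × 0.958)]² / 0.018²

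= [0.6098 + 0.2616]² / 0.000324 = 2,344 per arm, total 4,688.

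**Step 2: the same on the log risk ratio scale,** which matches the planned log-link analysis.

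n per arm = (1.960 + 0.8416)² × [(0.94/0.06) + (0.958/0.042)] / (ln 0.7)²

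= 7.849 × (15.667 + 22.810) / 0.1272 = 2,374 per arm, total 4,748.

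**Step 3: add 5% attrition by dividing by 0.95, and compare with 4,760.**

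| Formula (two-sided) | Evaluable total | With 5% attrition |
|---|---|---|
| Arcsine | 4,654 | about 4,899 |
| Unpooled | 4,682 | about 4,929 |
| Pooled | 4,688 | about 4,935 |
| Log risk ratio | 4,748 | about 4,998 |
| Continuity-corrected | 4,908 | about 5,167 |

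None of these reproduces 4,760 with the allowance included. Multiplying the pooled total by 1.05 instead of dividing by 0.95 gives 4,923, which does not either. A one-sided 5% test gives 3,694 evaluable, about 3,889 with attrition, which is well below 4,760. The nearest match is the log risk ratio total without attrition, 12 children away.

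**Step 4: how much loss 4,760 can absorb at 80% power.**

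- Pooled: 1 − 4,688/4,760 = 1.5%.
- Log risk ratio: 1 − 4,748/4,760 = 0.3%.

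**Step 5: power after the stated 5% loss.** 4,760 × 0.95 = 4,522 evaluable, 2,261 per arm.

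Pooled: [0.018 − 1.960 × √(2 × 0.051 × 0.949 / 2,261)] / √((0.06 × 0.94 + 0.042 × 0.958) / 2,261) = 0.792, so power = 78.6%.

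| Method | 4,522 evaluable | 4,760, no loss |
|---|---|---|
| Pooled | 78.6% | 80.6% |
| Log risk ratio | 78.1% | 80.1% |
| Arcsine | 78.9% | 80.9% |
| Continuity-corrected | 76.5% | 78.7% |
| Fisher exact | 76.8% | 79.0% |

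**Step 6: size of the gap.** In children: 4,688/0.95 − 4,760 = 174.7, or 3.7% of the stated total. In power: 80 − 78.6 = 1.4 points. In effect size: with 2,261 per arm, 80% power (pooled) is reached at a relative reduction of 30.5%.

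**Step 7: omphalitis, as a check on the same section.** 11.5% against 0.7 × 11.5% = 8.05%, with 2,261 per arm: power is 97.4% (pooled) or 97.2% (log risk ratio), against 96% stated.

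**The case against.** The strongest defence is that the discrepancy lies within the precision of the inputs. The control risk and the reduction are given as whole percentages, and no formula is named. A control risk of 6.2%, which would be printed as 6%, gives about 4,766 with the full 5% allowance by the pooled formula. The arcsine total is within 3% of 4,760. A condensed article may also leave the formula and software to the full protocol. This stands as an argument about size: a gap of 1.4 points of power changes no design decision, and the 6% itself is uncertain by more than 0.2 points. It does not make the printed sentence right, because the printed inputs do not yield the printed total and nothing in the article shows that other values were used.

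It could also be said that the intention-to-treat analysis includes all randomized infants, so attrition does not matter. But the article itself says that its calculation allows for attrition, and the statement has to hold on those terms.

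Three stronger readings are tempting and are not supported.

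- A reader might infer that 80% power holds only if no child is lost. On the pooled formula it survives about 1.5% loss, so part of an allowance is there, though not 5%.
- A reader might infer that the omphalitis power is a second error. The stated 96% is less than 2 points from 97.4% and errs on the cautious side, so it misleads no one to the trial's detriment.
- A reader might infer that the trial is materially underpowered for severe illness. A null result would be read in much the same way at 78.6% as at 80%.

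**Conclusion.** The point holds as a minor inconsistency in one stated figure. Under a two-sided 5% test, the inputs for severe illness require about 4,935 children enrolled (4,998 on the log risk ratio scale) to keep 80% power after 5% attrition, and the article states 4,760. At 4,760 enrolled and 5% lost, power is 78.6% (78.1% on the log risk ratio scale).

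The conclusion rests on two-sided testing, which is an assumption; with a one-sided 5% test 4,760 would be more than enough, but nothing in the article indicates one, and it would not reproduce the figure either. That 4,760 began as a total before attrition is a plausible explanation, given its closeness to 4,748, but the document does not establish it.

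**What to change.** Keep 4,760 and restate the objective 1 sentence in the Sample size section: with 5% attrition, 4,760 children give about 78–79% power to detect a 30% relative reduction from 6%, or equivalently 80% power to detect about a 30.5% reduction. Name the test or formula and state that the 5% type 1 error is two-sided, if it is. If a different formula or unrounded inputs produced 4,760, stating them would settle the point instead. The omphalitis sentence can stay as it is.

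The cost is one revised sentence. No extra children and no change to the analysis are needed; the stated power for objective 1 becomes slightly less favourable.
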